### 12.9. Emergency Procedures

During vaccination, staff trained in basic life support will be available in case of adverse reactions around vaccination. An emergency kit will also be available and checked routinely.

### 12.10. Pregnancy

Pregnancy will be actively assessed at baseline and 28 days post vaccination. Female participants becoming pregnant during the first 28 days following vaccination will be followed until the end of the pregnancy and the outcome will be recorded. This will be reported as an AE as the vaccine is not recommended in pregnant women. The outcome of the pregnancy (live birth, still birth or abortion) will be recorded after birth. Subsequent reports containing follow-up information regarding a pregnancy is not required unless the pregnancy results in a congenital anomaly. The congenital anomaly should be promptly reported as a Serious Adverse Event.

### 12.11. Procedures for reporting any protocol violation(s)

Protocol violations will be reported to the sponsor, regulatory and ethics committees as specified in their guidelines.

## 13. STATISTICS

### 13.1. Determination of sample size

This study will be powered to detect non-inferiority of each lower dose of vaccine (1000 IU, 500 IU, 250 IU) compared to the full standard vaccine dose. Sample size calculations were done using art2bin on Stata version 15.

For the adult study, we assumed a 95% seroconversion rate, 90% power, 2.5% alpha for a one-sided test and a non-inferiority margin of 10%, which gave a sample size of 100 per arm. The 10% non-inferiority margin was chosen in consideration of the public health consequence of a loss of protection but a potential increase in vaccine dosages in a situation where vaccine stocks are insufficient to respond to an outbreak. The sample size was increased by 20% to account for: i) losses to follow up and, ii) unevaluable participants with a positive serological response for YF virus at baseline. Thus, a total sample size of 480 will be required for the four vaccine dose groups (i.e. full dose, 1000 IU, 500 IU and 250 IU; Table 5).

For the study in children, we assumed a 90% seroconversion rate (accounting for lower vaccine immunogenicity reported in children [4]), 90% power, 2.5% alpha for a one-sided test and a non-inferiority margin of 10%, which gave a sample size of 190 per arm. This was increased by 10% to account for 5% losses to follow up and 5% unevaluable participants with a positive serological response for YF virus at baseline. This gave a total sample size of 420 (i.e. 210 in the full dose group and 210 in the lower dose group; Table 5).

Analyses of all other efficacy and safety endpoints are secondary outcomes. Therefore, no significance adjustments will be made for multiple comparisons.

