## **8. TRIAL DESIGN**

### **8.1. Overall Study Design and Plan Description**

This will be a parallel group, randomized, controlled, blinded, non-inferiority trial of four different doses of YF vaccine. The study will be conducted at the KEMRI CGMRC in Kilifi, Kenya and at Epicentre in Mbarara, Uganda. Both these sites are already working together in an ongoing study (Clinicaltrials.gov number: NCT02991495).

Adult participants (n=480) will be randomized for vaccination with full standard dose or with 1000, 500 or 250 IU (i.e. 4 arms) with a 1:1:1:1 allocation ratio. Results for the safety and primary outcome of the adult study will then be reviewed by the DSMB, and the lowest non-inferior dose in the adult study selected for assessment in children aged 9 to 12 months (n=420) in comparison to full standard dose (i.e. 2 arms), when co-administered with the EPI Measles vaccine, with a 1:1 allocation ratio. The determination of the non-inferior dose to use in children will be made by the sponsor in discussion with the study DSMB, vaccine manufacturer and relevant stakeholders, and the final decision communicated to the various regulatory authorities as a notification (i.e. SERU, OXTREC and PPB for the Kilifi site, MUST-REC, UNCST and NDA for the Mbarara site).

Adult vaccinees will be followed up for 2 years, and children for 1 year. There will be no gradual age de-escalation on the basis that there are few safety concerns with the full dose of YF vaccines, having been used in millions of children worldwide. The study procedures will be similar across both sites and these are summarized in Table 2.

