### 13.2.3. *Analysis of immunological endpoints*

Information for each of the following categories will be presented for the adult study and the children sub-study: number of individuals screened for eligibility; the number and reason of screen failures; the number and percentage of eligible individuals who consent and are randomized; the number and percentage of randomized individuals who receive a vaccine; the number and percentage of vaccinated individuals who complete a day 10 post-vaccination visit; the number and percentage of vaccinated individuals who complete a day 28 visit; the number and percentage of vaccinated individuals who complete a 12 month visit; the number and percentage of vaccinated individuals who complete a 24 month visit; the number and percentage of vaccinated individuals who complete the final analysis period (defined as completing all study activities up to 12 months for the children sub-study, and up to 24 months for the adult study); and the number of individuals who discontinue and the reason for discontinuation. Participant demographics and baseline characteristics will be described and compared between vaccine groups using non-parametric tests.

The intention to treat (ITT) population will comprise all randomized participants who received a dose of a study vaccine and that have at least one post-vaccination blood sample. The per protocol (PP) population will include randomized participants who have a blood sample at baseline and 28 days (+/- 3 days) post-vaccination, who are seronegative ( $\text{PRNT}_{50} < 1:10$ ) to YF at baseline, and for whom the eligibility criteria were correctly applied. The safety population will include all subjects who received a study vaccine.

The primary analysis will be a pairwise statistical comparison of the rate of seroconversion at day 28 between full dose and each lower dose of vaccine using a non-inferiority test with a margin of non-inferiority of 10% in the PP population. Seroconversion will be defined as a  $\geq 4$ -fold rise in  $\text{PRNT}_{50}$  titre between day 0 and day 28 samples. Any  $\text{PRNT}_{50}$  value reported as below the Limit of Quantification (LOQ) (e.g.  $< 1:10$ ) will be converted to  $\text{LOQ}/2$ . Thus a 4 rise for a subject who is  $< 1:10$  at baseline, is a titre of 20. Each immunogenicity assessment will be a pairwise comparison of the full dose and each lower dose within one study population (i.e. adults or children).

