### **3.2 Sample Size and Power Considerations**

This study will be powered to detect non-inferiority of each lower dose of vaccine (1000 IU, 500 IU, 250 IU) compared to the full standard vaccine dose.

For the adult study, assuming a 95% seroconversion rate, 90% power, 2.5% level of significance for a one-sided test and a non-inferiority margin of 10%, which gave a sample size of 100 per arm. The 10% non-inferiority margin was chosen in consideration of the public health consequence of a loss of protection but a potential increase in vaccine dosages in a situation where vaccine stocks are insufficient to respond to an outbreak. The sample size was increased by 20% to account for: i) losses to follow up and, ii) unevaluable participants with a positive serological response for YF virus at baseline. Thus, a total sample size of 480 will be required for the four vaccine dose groups (i.e. full dose, 1000 IU, 500 IU and 250 IU).

For the study in children, we assumed a 90% seroconversion rate (accounting for lower vaccine immunogenicity reported in children [4]), 90% power, 2.5% alpha for a one-sided test and a non-inferiority margin of 10%, which gave a sample size of 190 per arm. This was increased by 10% to account for 5% losses to follow up and 5% unevaluable participants with a positive serological response for YF virus at baseline. This gave a total sample size of 420 (i.e. 210 in the full dose group and 210 in the lower dose group).

Analyses of all other efficacy and safety endpoints are supporting only. Therefore, no significant adjustments will be made for multiple comparisons.

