#### *Primary Non-Inferiority Analysis*

The proportion of subjects who seroconvert will be presented by study arm for each study cohort, along with 95% confidence intervals. The primary analysis will be a pairwise statistical comparison of the rate of seroconversion at day 28 between full dose and each lower dose of vaccine using a non-inferiority test with a margin of non-inferiority of 10% in the PP population. Each immunogenicity assessment will be a pairwise comparison of the full dose and each lower dose within one study population (i.e. adults or children) using Dunnett's Test.

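### The adult sizing states 90% power at one-sided 2.5% with 100 evaluable per arm; score-type tests that hold that level at high control rates have about 83% exact power there, and the plan names no interval for the difference

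*Supplement*

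**What the plan says.** Protocol 13.1 gives the adult design inputs: "we assumed a 95% seroconversion rate, 90% power, 2.5% alpha for a one-sided test and a non-inferiority margin of 10" per cent, "which gave a sample size of 100 per arm". It adds that "Sample size calculations were done using art2bin on Stata version 15" but does not give the variance option. The inflation follows: "The sample size was increased by 20% to account for: i) losses to follow up and, ii) unevaluable participants" already seropositive for yellow fever, which makes 120 per arm and 480 in total. SAP 3.2 repeats the calculation in nearly the same words ("assuming a 95% seroconversion rate, 90% power, 2.5% level of significance for a one-sided test and a non-inferiority margin of 10" per cent).

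The analysis text does not say which test the power figure belongs to. Protocol 13.2.3 specifies a "non-inferiority test with a margin of non-inferiority of 10% in the PP population". SAP 5.3.2 says the comparison is made "using a non-inferiority test with a margin of non-inferiority of 10% in the PP population" and then names Dunnett's test for the pairwise comparisons. SAP 5.1.1 says there will be no adjustment for multiple comparisons, because one confidence interval is built per lower dose. Neither document names an interval or variance method for a difference of two proportions.

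**The concern.** With 95% seroconversion and 100 per arm, about five non-responders per arm are expected. The normal approximation with unpooled variance is known to be unreliable there, and methods that agree at moderate rates give different answers. The stated power and alpha may therefore not describe any one test the trial could run.

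The primary comparison decides whether each lower dose is called non-inferior, and under SAP 3.4 it also guides which dose goes forward to the infant study. If power is lower than stated, a truly equivalent dose is missed more often than the planned 10%. If an anti-conservative interval is used, a dose 10 points worse passes more often than 2.5% of the time. Because no method is named, the result could turn on a choice made after the data are seen.

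**Working it through.** **Inputs.** Seroconversion 95% in both arms, margin 10 points, one-sided alpha 2.5%, power 90%, 100 evaluable and 120 randomised per arm (protocol 13.1 and Table 5; SAP 3.2). Allocation is equal: "500 or 250 IU (i.e. 4 arms) with a 1:1:1:1 allocation ratio" (protocol 8.1).

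**Step 1: reproduce the plan's figure.** Unpooled normal formula:

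n = 2 × 0.95 × 0.05 × (1.960 + 1.2816)² / 0.10² = 0.095 × 10.508 / 0.01 = 99.8, so 100 per arm.

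The same formula for children gives 2 × 0.90 × 0.10 × 10.508 / 0.01 = 189.1, so 190, also as stated. The arithmetic is right. That this formula was used is inferred from the two matches.

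**Step 2: a formula using the variance under the null.** The Farrington-Manning constrained estimates at the margin are 0.8703 and 0.9703:

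n = [1.960 × √(0.8703 × 0.1297 + 0.9703 × 0.0297) + 1.2816 × √0.095]² / 0.01 = (0.738 + 0.395)² / 0.01 = 128.3, so 129 per arm.

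**Step 3: exact enumeration.** All pairs of binomial counts were enumerated. Non-inferiority is declared when the lower limit of the two-sided 95% interval for lower dose minus full dose exceeds -0.10, with no multiplicity adjustment. Power is at 95% versus 95%. Size is at a full-dose rate c and a lower-dose rate c minus 10 points.

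| Method, n = 100 per arm | Power | Size, 95 vs 85 | Size, 99 vs 89 |
|---|---|---|---|
| Farrington-Manning, Miettinen-Nurminen, Newcombe | 83.2% | 2.31% | 1.96% |
| Wald | 88.6% | 3.39% | 4.14% |
| Hauck-Anderson | 87.0% | 2.36% | 4.12% |

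Hauck-Anderson holds 2.5% at the design null, but its size is 2.59% at a control rate of 96% and 2.97% at 97%. Of the others examined, likelihood ratio (86.0% power, size 2.74%) and Agresti-Caffo (87.4%, 2.82%) exceed the level at 95 versus 85. Chan's exact test (81.1%) and continuity-corrected Wald (82.7%, size 1.8% at 95 versus 85) stay within 2.5% there. None combines 90% power with a 2.5% level.

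**Step 4: number evaluable.** The 20% was applied as 100 × 1.2 = 120. Losing 20% of 120 leaves 96.

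| Evaluable per arm | Farrington-Manning power | Newcombe power |
|---|---|---|
| 96 | 81.1% | 81.1% |
| 100 | 83.2% | 83.2% |
| 108 | 86.7% | 86.8% |
| 112 | 86.8% | 88.2% |
| 120 | 89.0% | 90.1% |

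Farrington-Manning first reaches 90% at 122 evaluable per arm.

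**Step 5: true rate.** At n = 100, score-test power is 83.2% at a true rate of 95%, 88.4% at 96% and 93.3% at 97%.

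**Step 6: if Dunnett's test means an adjusted critical value.** For three one-sided comparisons with correlation 0.5 the critical value is 2.349. Power at n = 100 is then 68.1% for the score test and 82.5% for Wald.

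**Step 7: the choice can change a result.** Take 92/100 on a lower dose and 95/100 on full dose; the difference is -0.03.
- Wald: standard error √(0.92 × 0.08/100 + 0.95 × 0.05/100) = 0.0348; lower limit -0.03 - 1.96 × 0.0348 = -0.098, which passes.
- Newcombe: the Wilson lower limit for 92/100 is 0.850 and the upper limit for 95/100 is 0.978; lower limit -0.03 - √(0.070² + 0.028²) = -0.106, which fails.

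The pairs 93 v 96, 94 v 98 and 95 v 99 also pass by Wald and fail by Newcombe.

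**The case against.** The strongest reply is that nothing is miscalculated. The inputs give 100 by a standard formula, and the gap is between a large-sample approximation and exact behaviour. That is correct: this is not an arithmetic slip.

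The shortfall also depends on circumstances. The inflation covers losses and baseline seropositivity together, and power is about 86-88% with 108 to 112 evaluable. The documents themselves cite rates above 95%: 99% within a month (protocol 5.2) and 97.7% at 587 IU (protocol 5.5). At 97.7%, score-test power with 100 per arm is 96.3%. This stands as a limit on how much power is lost in practice. It does not make the printed statement right at its own assumptions, and high control rates are where Wald's false-positive rate is worst.

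A reader might infer that the trial will run at a 3.4-4.1% false-positive rate. The documents do not support that: no passage says a Wald interval will be used, and a sizing formula does not fix the analysis method. A reader might also infer that every test holding 2.5% is confined to 81-83% power. Hauck-Anderson holds the level at the design null with 87.0%, though not at control rates of 96% or above.

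**Conclusion.** At the plan's own assumptions, 90% power at one-sided 2.5% is not delivered by 100 evaluable adults per arm. Score-type intervals that hold the level at high control rates give 83.2%, so the chance of missing a truly equivalent dose is about 17% rather than 10%; at 96 evaluable it is about 19%. With all 120 evaluable the shortfall nearly disappears.

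These figures assume 95% seroconversion in both arms and unadjusted comparisons. The false-positive figures for Wald describe what would happen if that interval were chosen. The plan leaves that choice open, and this open choice is the part that can affect the primary conclusion. The power restatement alone is a matter of accurate disclosure. The children's figure is nearly right: 190 per arm gives 88.5% (Farrington-Manning) to 89.0% (Newcombe).

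**What to change.** - **SAP 5.3.2:** replace the unspecified non-inferiority test with a stated criterion: the lower limit of a score (Farrington-Manning/Miettinen-Nurminen) or Newcombe interval for lower dose minus full dose lies above -10 percentage points. Name one of these and state that the Wald interval will not be used.
- **SAP 5.3.2 and 5.1.1:** reconcile the reference to Dunnett's test with the statement that no multiplicity adjustment is made. The confidence level of the interval follows from that decision; two-sided 95% applies only if the comparisons are unadjusted.
- **Protocol 13.1 and SAP 3.2:** restate adult power for the chosen test and multiplicity rule. If unadjusted: about 83% at 100 evaluable per arm, 81% at 96 and 89-90% at 120. If a Dunnett-type critical value is kept: about 68% at 100.

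Enrolment does not change, and the intervals can be computed in the software the SAP lists. The only cost is a less favourable stated power.

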**Table 5: Planned participant recruitment numbers in Kilifi and Mbarara**

| Population          | Allocation       | Participants in Kilifi (n) | Participants in Mbarara (n) | Total per allocation |
|---------------------|------------------|----------------------------|-----------------------------|----------------------|
| Adults
(N=480)   | Full dose        | 60                         | 60                          | 120           |
|                     | 1000 IU          | 60                         | 60                          | 120           |
|                     | 500 IU           | 60                         | 60                          | 120           |
|                     | 250 IU           | 60                         | 60                          | 120           |
| Children
(N=420) | Full dose        | 105                        | 105                         | 210           |
|                     | To be determined | 105                        | 105                         | 210           |

## 13.2. Statistical and analytical plans

### 13.2.1. Data management

A Data Management team will be located at each study site. Data collection will occur at each study site using standardized CRFs transported by designated staff. Data entry clerks will use password-protected computers. Data will be double entered at each study site.

The CRFs in this study will be entered onto an electronic database at each study site. This will be done via secure web interface with data checks used during data entry to ensure data quality. The database will be activated for the study only after successfully passing a formal design and test procedure. Laptops and desktop computers will be used for data entry of paper forms. Management and maintenance of computers will lie with the operational support and data managers at the study site.

### 13.2.2. Data security, access and backup

The database will be kept in a locked server-room. Only the system administrators have direct access to the server and back-up tapes. A role concept with personal passwords (site investigator, statistician, monitor, administrator etc.) regulates permission for each user to use the system and database, as he/she requires.

All data entered onto the CRFs are transferred to the database using Secure Sockets Layer (SSL) encryption. Each data point has attributes attached to it identifying the user who entered it with the exact time and date. Retrospective alterations of data in the database are recorded in an audit table. Time, table, data field and altered value, and the person are recorded (audit trail). A multi-level back-up will be implemented. Back-ups of the entire system including the database are run internally several times per day and on external tapes once a day. The back-up tapes are stored in a secure location.

### 13.2.3. *Analysis of immunological endpoints*

Information for each of the following categories will be presented for the adult study and the children sub-study: number of individuals screened for eligibility; the number and reason of screen failures; the number and percentage of eligible individuals who consent and are randomized; the number and percentage of randomized individuals who receive a vaccine; the number and percentage of vaccinated individuals who complete a day 10 post-vaccination visit; the number and percentage of vaccinated individuals who complete a day 28 visit; the number and percentage of vaccinated individuals who complete a 12 month visit; the number and percentage of vaccinated individuals who complete a 24 month visit; the number and percentage of vaccinated individuals who complete the final analysis period (defined as completing all study activities up to 12 months for the children sub-study, and up to 24 months for the adult study); and the number of individuals who discontinue and the reason for discontinuation. Participant demographics and baseline characteristics will be described and compared between vaccine groups using non-parametric tests.

The intention to treat (ITT) population will comprise all randomized participants who received a dose of a study vaccine and that have at least one post-vaccination blood sample. The per protocol (PP) population will include randomized participants who have a blood sample at baseline and 28 days (+/- 3 days) post-vaccination, who are seronegative ( $\text{PRNT}_{50} < 1:10$ ) to YF at baseline, and for whom the eligibility criteria were correctly applied. The safety population will include all subjects who received a study vaccine.

The primary analysis will be a pairwise statistical comparison of the rate of seroconversion at day 28 between full dose and each lower dose of vaccine using a non-inferiority test with a margin of non-inferiority of 10% in the PP population. Seroconversion will be defined as a  $\geq 4$ -fold rise in  $\text{PRNT}_{50}$  titre between day 0 and day 28 samples. Any  $\text{PRNT}_{50}$  value reported as below the Limit of Quantification (LOQ) (e.g.  $< 1:10$ ) will be converted to  $\text{LOQ}/2$ . Thus a 4 rise for a subject who is  $< 1:10$  at baseline, is a titre of 20. Each immunogenicity assessment will be a pairwise comparison of the full dose and each lower dose within one study population (i.e. adults or children).

Secondary analyses will include assessment of seroconversion in the ITT population as a whole, on the subset of the ITT population with baseline seropositivity to YF, and in the subset of the PP population with no reported history of flavivirus infection. Geometric mean  $\text{PRNT}_{50}$  titre (GMT) and GMT fold increase (GMFI) and corresponding 95% confidence intervals (CI) on day 0 and 28 will be calculated. A test of non-inferiority will be performed for the difference in GMT and GMFI between the full dose and each lower dose group. Titres will be graphically represented by reverse cumulative distributions obtained by plotting, for each possible value of the titre (abscissa), the proportion of subjects with a titre greater than this value.

Lower vaccine doses may change the kinetics of antibody response. The assessment of seroconversion rates, GMT, and GMFI 10 days after vaccination in the ITT population will provide important information in the context of low dose vaccine usage in outbreak response. These three immunogenicity outcomes will also be assessed at 1 year and 2 years post-vaccination in the ITT population to confirm a lasting effect of full and low dose vaccination.

Relationships between seroconversion and vaccine immunogenicity ( $\text{PRNT}_{50}$  GMT and GMFI) will be related to frequencies of specific T and B cell subsets measured by flow cytometry, chemokine

and cytokine levels in sera and neutralising antibody levels to other flaviviruses. Correlations between vaccine viraemia and immunogenicity will be assessed across the different vaccine dose strata. Comparisons of these immune and viraemia kinetics will be made between the adult and children trial participants, whilst accounting for the administered vaccine dose.

Adverse events occurring during the study follow up period will be analysed and compared between groups. This will be a descriptive analysis and will include all AEs up to 28 days post-vaccination, and SAEs that occurred any time during study follow-up.

A detailed statistical analysis plan (SAP) will be provided separately and finalized after the study has started (and before the database lock). This SAP will include all conventions on data, descriptive and statistical analyses to be performed on collected data during the conduct of the study.

